### Primary outcomes

Given SECURE is a service evaluation with a range of study objectives, there will not be an overall pre‐specified primary outcome for the entire study – each survey will have its own defined primary outcome, as follows:Site Survey – proportion of clinical areas meeting an essential RSI resource standard (RSI preparedness);Vignette‐based Survey – the proportion of respondents with any change from baseline in their selection of RSI components across clinical vignettes;Activity Survey – proportion of RSI events with first attempt success at tracheal intubation and without immediate complications related to airway management.

The Site Survey was completed by investigator teams at all registered study sites during a 6‐week data collection window (01/03/2026 to 12/04/2026). The Vignette‐based survey will be open for practitioner responses over a seven week period between 13/07/2026 and 30/08/2026. During the Activity Survey, prospective data was collected by intubating teams over a continuous 14‐day period within a broader data collection window (13/04/2026 to 25/05/2026). Exact dates were agreed at each study site to enable simultaneous data collection across all clinical areas locally. We will aim to complete full data analysis and reporting sequentially for all three surveys by mid‐2027.

The study surveys will be publicised and delivered widely through the SECURE investigator network at a local level. We will target an 80% response rate for the Site Survey per clinical area (> 500 responses in total). The Vignette‐based Survey will be distributed across all sites, with a target of at least 5% of eligible practitioners (> 1300 responses). A final response rate will be calculated using data from NHS bodies and colleges – approximately 27,000 practitioners work across anaesthesia, ICM and EM. We assume all will be eligible apart from a small number of residents who have not achieved their competency in RSI (Supporting Information, Appendix S2).

We estimate around 7400 in‐hospital adult RSI events (approximately 25% out‐of‐theatre) occur UK‐wide in a typical 14‐day period. This number is extrapolated from previous UK‐based studies, including large snapshot surveys, which suggest RSI rates are reproducible by time and place (Supporting Information, Appendix S3) [9]. The denominator for the survey will be scaled to registered sites – targeting > 10% capture (> 740 RSI events, assuming all eligible sites participate).

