### Data management

Data collected for all three surveys will be uploaded promptly to a central, secure REDCap database at the study Sponsor site. After submission, to ensure compliance with data protection and information governance standards, no patient‐identifiable information will be accessible by local teams. Database access will be restricted to selected members of the SECURE Investigation Group, who will monitor the data regularly for accuracy and completeness.

The study statistician will undertake data cleaning for each survey once data collection is complete. Fully completed case report forms will be included in the final analysis, while incomplete or duplicate submissions will be excluded. Where possible, local teams will be asked to report duplications and errors centrally by email to assist in identification by site, date and time stamp. Where there is any uncertainty around the inclusion of a case report form response in analysis, the investigation group will make a final decision on a case‐by‐case basis.

Our project statistician has reviewed the design of each survey case report form to ensure consistency with the planned statistical analysis. As a descriptive service evaluation, no formal sample size calculation was performed. After analysis, data will be archived in accordance with the information governance policy of the Sponsor site for a maximum of five years, with the Chief Investigator acting as the custodian.

Initially, a basic descriptive analysis will be undertaken for all three surveys, including absolute numbers and percentages within categorical groups and medians (IQR), where applicable. We will report our outcomes, summarise responses to survey questions, identify themes and consensus points and explore variability in responses. Of interest, we will report by sub‐groups cross‐speciality, between different types of NHS hospitals and regions in the UK.

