An additional analysis plan for the Vignette‐based Survey and Activity Survey will be determined in advance. All tests will be two‐tailed, and where possible, odds ratios, 95% confidence intervals (CI) and actual p‐values (with significance assumed at p < 0.05) will be reported as appropriate. Methods will include the Chi‐squared test or exact tests, as appropriate. We will aim to perform pre‐specified regression analyses for the Activity Survey relating risk factors (situation, patient and technical factors) and immediate complications, with 95% CI and p‐values, where possible, including factors associated with the outcomes. The analysis of vignette responses will describe within‐person variability, rather than inter‐individual variability, with pre‐agreed statistical significance testing.

SECURE will not involve any study intervention or any change to concomitant care; therefore, there is no direct risk of patient harm. All elements of the study have been discussed with the NHS Health Research Authority (HRA), which advised that the project is not considered as research, can be classified as a service evaluation and does not require ethical approval. No patient identifiable data will be collected; therefore, patient consent is not required.

In England and Wales, Confidential Advisory Group (CAG) approval is not required, as confirmed using their online checklist [29]. In Scotland, the Electronic Data Research and Innovation Service (eDRIS) team at Public Health Scotland has advised that Public Benefit and Privacy Panel for Health and Social Care (PBPP) permission is not required. In Northern Ireland, SECURE has been approved as a service evaluation by the Health and Social Care Privacy Advisory Committee, with Data Access Agreement (DAA) forms completed for every Health and Social Care Trust.

The project has been reviewed, approved and registered as a service evaluation with the Information Governance department and Caldicott Guardian at the Sponsor site, University Hospitals Bristol and Weston (UHBW), Bristol, UK. Site leads will be mandated to provide evidence of study registration with the Information Governance department at each site before commencing data collection.

Pooled, non‐identifiable results from SECURE will be disseminated as widely as possible in the UK and internationally, through relevant bodies and our collaborators (DAS, SIVA, TRIC, TERN, RCoA and RCEM) to maximise impact and accessibility.

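### Forms of uncertain eligibility are decided case by case, with no stated criterion or outcome masking, by a group whose selected members can see the data

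*Protocol article*

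**What the plan says.** All the operative text is in the Data management section of the protocol article and applies to all three surveys.

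- Cleaning: "The study statistician will undertake data cleaning for each survey once data collection is complete".
- Default rule: "Fully completed case report forms will be included in the final analysis, while incomplete or duplicate submissions will be excluded".
- Residual cases: "Where there is any uncertainty around the inclusion of a case report form response in analysis, the investigation group will make a final decision", and it does so case by case.
- Access: "Database access will be restricted to selected members of the SECURE Investigation Group, who will monitor the data regularly for accuracy and completeness".

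The same section says that no patient-identifiable data are collected. Local teams are asked, where possible, to report duplicates and errors, which are then traced by site, date and time stamp. Table 1 counts a repeat RSI in the same patient as a new event. Under Primary outcomes, the Activity Survey outcome is the proportion of RSI events with first-attempt success and no immediate airway-related complication.

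**The concern.** The body that settles doubtful inclusions contains people who can see the records, including whether intubation succeeded first time and what complications followed. As the article is written, they have no rule to apply and nothing hides those fields from them. Knowledge of the result could influence a decision to keep or drop a form without anyone intending it.

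The Activity Survey is the most exposed. Its primary outcome is a proportion whose numerator and denominator are both set by inclusion. Its design can also produce forms that are hard to classify: a true second RSI in one patient counts, a second form for the same RSI does not, and no identifier separates the two. A shift arising this way would not show in the confidence interval, which reflects sampling error only.

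**Working it through.** **Route from discretion to result.** Three statements have to be read together.

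1. On uncertain forms, "the investigation group will make a final decision on a case‐by‐case basis".
2. Database access belongs to selected members of that group, "who will monitor the data regularly for accuracy and completeness".
3. The primary outcome is computed on the included events.

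No criterion and no masking appears between the first and the third. The route is therefore open as the rule is written.

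**Inputs for size.**
- From the article (Primary outcomes): about 7400 events in a typical 14 days, with a target capture above 10%. Check: 0.10 × 7400 = 740, which matches the stated figure.
- Assumed, because the article does not give them: N = 740 records; primary proportion p among the clear records of 0.60 to 0.90; doubtful share of 1%, 2%, 5% or 10%, giving m = 7, 15, 37 or 74.

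**Sampling precision.** Half-width = 1.96 × √(p(1 − p)/N).
- p = 0.60: 1.96 × √(0.24/740) = 3.5 points.
- p = 0.90: 1.96 × √(0.09/740) = 2.2 points.

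**Extreme swing.** With N − m clear records at proportion p, keeping m doubtful records that are all failures gives p(N − m)/N. Keeping m that are all successes gives [p(N − m) + m]/N. The difference is m/N whatever the value of p:
- 7/740 = 0.9 points
- 15/740 = 2.0 points
- 37/740 = 5.0 points
- 74/740 = 10.0 points

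**How the swing splits.** The swing is an outer bound, because it covers both possible sets of outcomes. For a given set, the contrast is between keeping and dropping. Dropping all m gives p, so keeping m failures lowers the result by p × m/N and keeping m successes raises it by (1 − p) × m/N. For m = 37:

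| p | Half-width (points) | All kept, all failures | All kept, all successes | Shift down / up (points) |
|---|---|---|---|---|
| 0.60 | 3.5 | 57.0% | 62.0% | 3.0 / 2.0 |
| 0.70 | 3.3 | 66.5% | 71.5% | 3.5 / 1.5 |
| 0.80 | 2.9 | 76.0% | 81.0% | 4.0 / 1.0 |
| 0.90 | 2.2 | 85.5% | 90.5% | 4.5 / 0.5 |

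At 5% doubtful, the full swing exceeds the half-width throughout the range. The one-sided downward shift exceeds it from p = 0.70 upward. At 2% doubtful, even the full swing of 2.0 points stays below the smallest half-width of 2.2.

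**The case against.** The other side has good points. The discretion is residual: it acts only after the default rule and the statistician's cleaning. Duplicates can be checked by site, date and time stamp, and Table 2 records age, sex, ethnicity, body size, ASA grade, indication and hospital area, so most repeat events should be separable from double entries. This is also a descriptive service evaluation with no allocated arms. All of that stands, and it limits the size of the problem. It supplies neither a criterion nor masking for the forms that remain.

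Four stronger readings are tempting, and the article does not support them.

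- **That doubtful forms will be common.** No count or rate is given. The checks above suggest only that some may arise.
- **That everyone who decides has seen the outcomes.** Access is limited to selected members. The article does not say that they are the ones who decide.
- **That the Activity Survey analysis plan was still unwritten after collection.** A reader might set "During the Activity Survey, prospective data was collected by intubating teams" beside the statement that the additional plan for the Vignette-based "Survey and Activity Survey will be determined in advance". Tense is a poor guide here: the article also says that the forms will be built, although two surveys are reported as already collected. It says too that the statistician has reviewed the forms against the planned analysis. A separate plan may exist and is not shown.
- **That the scope of the airway-complication composite is left to that plan.** Nothing in the article says so.

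A sharper example can also be built. Suppose overall failure is 20.0% (148/740), 15 of 37 doubtful forms are failures, and only those 15 are dropped. Failure becomes 133/725 = 18.3%. This assumes selection purely on outcome, and the 1.7-point shift is still inside the 2.9-point half-width. It is a constructed worst case and not an expected effect.

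**Conclusion.** The concern holds in a limited form. The article fixes case-by-case inclusion by a group that includes people with data access, and states no criterion or masking. This leaves an avoidable route to outcome-dependent selection. There is no evidence that the route has been or will be used.

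Its importance depends on the unknown share of doubtful forms. At 1–2% the extreme swing is about 1 to 2 points, below the 95% half-width of 2.2 to 3.5 points. At 5% it is about 5 points, above it. These figures assume 740 events, a primary proportion of 0.60 to 0.90 and independent events. Clustering of events within sites would usually widen the interval, and fewer captured events certainly would; neither changes the swing for a given doubtful share. The change is worth making because it is cheap, but the finding does not by itself undermine the study.

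**What to change.** Replace the case-by-case decision with a short written rule, for all three surveys, on what counts as complete, duplicate or eligible. For the Activity Survey, base it on fields already collected: site, area, date and time stamp, age, sex and indication. Apply it to an extract in which first-attempt success and complications are hidden. Log each decision with its reason, report the number of excluded forms and why, and run a sensitivity analysis that includes all doubtful forms. If any decisions have already been made unmasked, log and report them as such.

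The cost is a masked REDCap export and one extra analysis, with no new data. One limitation remains: a form that is doubtful only because its outcome fields conflict cannot be judged with those fields hidden, so it needs a separate logged query. Nobody with database access has to be barred from writing the analysis plan; that could exclude the statistician who cleans the data.

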## Conclusion

Despite decades of changing clinical practice, many of the techniques and some of the equipment used in RSI have a limited evidence base. Surveys suggest widespread variation in practice but are potentially limited by discrepancies between self‐reported and actual behaviour.

SECURE is a national, resident‐led, prospective service evaluation which will characterise contemporary RSI in adults across NHS hospitals in the UK in the settings of anaesthesia, ICM and EM. The outcomes of the project are expected to influence national and international practice through updates to terminology, clinical opinion, research priorities and recommendations.
